##### Clinical and cognitive

For clinical assessments and the Go/No Go task, between-group differences over time will be examined using a linear mixed-effects model approach. Follow-up scores for each outcome will be included as dependent variables, and baseline and treatment allocation values will be included as fixed-effect predictors. Time points will be included as a fixed factor. To account for the correlation between repeated measurements from the same participant, a random intercept will be included at the participant level.

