#### Clinical

The CGI severity [65] and improvement assessments include an interview by the physician with the participant and caregiver. Parent-reported measures include the Aberrant Behaviour Checklist (ABC) [66, 67], Emotional Dysregulation Inventory (EDI) [68, 69], Autism Impact Measure (AIM) [70], and Emotional Regulation Checklist (ERC) [71]. These measures have been validated in youth with ASD and will indicate clinical treatment-related improvement. The ABC has excellent reliability and was specifically designed to measure treatment effects on aberrant behaviors, with extensive application in previous ASD trials [72]. The EDI-reactivity scale measures poorly regulated negative emotions, and the EDI-dysphoria scale measures minimal positive affect and motivation. The AIM measures treatment-related improvements in children with ASD across several ASD symptom domains [70]. The ERC measures emotional regulation and is sensitive to a broad range of regulatory processes [73].

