#### Neural

At the baseline assessment (T0), participants will undergo optional high-resolution MRI on a Siemens 3 T Prisma MRI. Structural T1-MPRAGE, DTI, and resting-state functional MRI data will be collected at all time points (T0–T2). Acquisition of neuroimaging data will allow for the investigation of changes at immediate post-treatment (T1) and maintenance at long-term follow-up (T2).

At the baseline assessment, participants will undergo an optional high-resolution MRI on a Siemens 3 T Prisma MRI. Structural (T1 and diffusion tensor imaging) and resting-state functional MRI data will be collected at all timepoints. Acquisition of neuroimaging data will allow for the investigation of changes at immediate post-treatment and maintenance at long-term follow-up.

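### The mixed model listed for the clinical and Go/No Go outcomes has no treatment-by-time term, so it gives one group difference common to T1 and T2 and cannot show how that difference changes.

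*Protocol article*

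**What the plan says.** The specification is in the Protocol article, Data analysis, Secondary measures analysis, Clinical and cognitive. It has four parts:

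- Aim: "between-group differences over time will be examined using a linear mixed-effects model approach".
- Outcome: "Follow-up scores for each outcome will be included as dependent variables". T1 and T2 are therefore the only modelled responses, and T0 enters on the right-hand side.
- Fixed effects: "baseline and treatment allocation values will be included as fixed-effect predictors. Time points will be included as a fixed factor".
- Random effect: "a random intercept will be included at the participant level".

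Neither this section nor any other part of the article names a treatment-by-time product, a visit-specific contrast or a separate model per visit. The analysis serves the first secondary objective (Secondary outcome measures), which is to estimate the likely effect of tDCS on clinical, cognitive and neural outcomes.

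**The concern.** The aim and the list of terms do not match. Examining how a group difference behaves over time needs a parameter that lets it differ between visits, and the list contains none. In designs where T0 is one of the modelled responses, a group-by-time term is the usual carrier of the treatment effect. Here T0 is a covariate, so the treatment main effect takes that role and is forced to be equal at T1 and T2.

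At stake is what the exploratory analysis can say. An effect present at T1 and gone by T2, an effect that appears only at T2, and a smaller steady effect would all be summarised by one similar number. The Discussion presents longer follow-up as a strength of the design, so a model that cannot separate the two follow-up visits leaves part of that information unused.

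**Working it through.** The article gives no figure for this model, so there is none to reproduce. The structural result is algebra. The numbers illustrate its size under stated assumptions.

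**1. Model as listed.** Let i be the child and t the visit (T1 or T2):

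E[Y_it] = b0 + b1·baseline_i + b2·trt_i + b3·I(t = T2)

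Active minus sham at T1 is b2. Active minus sham at T2 is (b2 + b3) − b3 = b2. The random intercept has mean zero and does not alter this. The equality holds for any SD, correlation or sample size.

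**2. Model with the interaction.** Add b4·trt_i·I(t = T2). The difference is b2 at T1 and b2 + b4 at T2, and the change is b4.

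**3. Inputs for the illustration.**
- From the article: n = 46 and 1:1 allocation, so 46/2 = 23 per arm; 10% loss, applied at T2.
- Assumed: outcome SD 1, correlation 0.5 between any two visits, and the true effects in the table.
- Method: random-intercept model by REML, 150 simulated trials per row. Entries are the mean estimate, with the mean standard error in brackets.

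| True effect T1 / T2 (SD) | Listed model, single effect | With interaction, T1 | With interaction, T2 | T2 minus T1 |
|---|---|---|---|---|
| 0.5 / 0.5 | 0.466 (0.215) | 0.457 (0.256) | 0.476 (0.268) | 0.019 (0.298) |
| 0.5 / 0 | 0.257 (0.214) | 0.477 (0.257) | 0.004 (0.270) | −0.473 (0.305) |
| 0.25 / 0.25 | 0.233 (0.214) | 0.247 (0.256) | 0.219 (0.270) | −0.028 (0.303) |
| 0.5 / −0.5 | 0.035 (0.212) | 0.490 (0.255) | −0.484 (0.267) | −0.975 (0.304) |

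The Monte Carlo error of a mean in the second column is about 0.214/√150 = 0.017. The gap between 0.257 and 0.233 (0.024) is therefore of the order of simulation noise, and far smaller than the standard error of 0.214 in a single trial. Effects of opposite sign nearly cancel (0.035). A constant effect is recovered up to simulation noise.

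**4. Check of the standard errors by formula, and their range.** With correlation ρ and SD 1, conditioning on baseline leaves variance v = 1 − ρ² at each visit and covariance c = ρ − ρ² between visits. With complete data and 23 per arm:

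- one visit: SE = √(v·2/23)
- average of both visits: SE = √(((v + c)/2)·2/23)
- change between visits: SE = √(2(v − c)·2/23)

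At ρ = 0.5, v = 0.75 and c = 0.25. This gives √(0.75·2/23) = 0.255, √(0.50·2/23) = 0.209 and √(1.00·2/23) = 0.295. The simulated values are slightly larger, as expected with 10% missing at T2 and an estimated baseline slope.

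| ρ (assumed) | v | c | SE, one visit | SE, average | SE, change | One visit / average |
|---|---|---|---|---|---|---|
| 0.3 | 0.91 | 0.21 | 0.281 | 0.221 | 0.349 | 1.27 |
| 0.5 | 0.75 | 0.25 | 0.255 | 0.209 | 0.295 | 1.22 |
| 0.7 | 0.51 | 0.21 | 0.211 | 0.177 | 0.228 | 1.19 |

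A visit-specific interval is thus roughly 19% to 27% wider than the interval for the average.

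**The case against.** The strongest reply is that a short article names variables rather than a full model formula, that the opening sentence itself announces a group-by-time comparison, and that an unseen analysis plan may contain the interaction. The last part may well be true. But the article does more than stay silent: it lists the outcome, the fixed effects and the random effect, and that list does not deliver the aim in the same paragraph. The mismatch is in the text shown.

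A second reply is that the average effect is legitimate and more precise. That stands. With 46 children, the change between visits would be estimated poorly in any case (SE about 0.30 in the simulation). This argues for wide intervals honestly reported, or for stating that an average is what is wanted. It does not reconcile the model with its stated aim.

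Stronger readings are tempting, but the document does not support them:

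- **The effect will be reported as halved.** Halving follows only from assuming a full effect at T1 and none at T2. Under a constant effect there is no distortion.
- **The future trial's timepoint or effect size will be set wrongly.** No section ties this coefficient to either. The hypothetical size of 100 comes from previous neurostimulation trials (Primary outcome measures), and Sample size says that pilots do not test efficacy.
- **The protocol sets a maintenance aim for these outcomes.** The wording "changes at immediate post-treatment (T1) and maintenance at long-term follow-up (T2" stands in the Neural section and concerns imaging, which has its own analysis paragraph. The Discussion's remarks on longitudinal data end in a feasibility question.
- **A baseline × time term is also needed.** No stated aim requires it.
- **The model cannot be fitted to CGI improvement for want of a baseline value.** The article says only that the severity and "improvement assessments include an interview by the physician with the participant and caregiver". It does not describe how the improvement rating is scored or whether a T0 value exists.

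**Conclusion.** The point holds as a mismatch between a stated aim and a stated model. By construction, the terms listed under Clinical and cognitive give one active-minus-sham difference for both T1 and T2. This needs no numerical assumption. The estimate is a valid baseline-adjusted average over follow-up and is informative as such, but it says nothing about change between visits or about either visit alone.

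The practical size depends on how far the effects at the two visits differ, which the documents cannot tell us. Under the assumed values it ranges from no loss (constant effect) to near-complete cancellation (0.5 and −0.5 SD returned as about 0.04). These outcomes are secondary and exploratory. Table 1 uses recruitment, adherence, retention and MRI completion only, so the decision to proceed is not touched. The change is worth making because it is cheap and brings the model into line with its aim.

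**What to change.** Add treatment × time as a fixed effect in the Clinical and cognitive model. Report the adjusted group difference with its 95% confidence interval at T1 and at T2. If one summary is also wanted, report the average over both visits as a contrast from the same model. Alternatively, if only an average was ever intended, say so and reword the aim.

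The cost is one line of text and somewhat wider visit-specific intervals: SE about 0.26–0.27 against 0.21 for the average, under SD 1 and correlation 0.5. The average stays available from the same fit at about its present precision. No extra data, visits or participants are needed.

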### Participants

#### Recruitment

Children with ASD with self-regulation impairments (*n* = 46) aged 9–18 years will be recruited from the Province of Ontario Neurodevelopmental Disorders Network (POND) (www.pond-network.ca). The lower limit of nine years old was determined based on previous studies investigating the safety and tolerability of non-invasive brain stimulation (NIBS) in children with ASD [24, 25]. POND participants have an existing research-reliable ASD diagnosis based on DSM-V criteria, informed by the gold standard Autism Diagnostic Observation Schedule (ADOS) [22] and the Autism Diagnostic Interview – Revised (ADI-R) [26]. Recruitment flyers will be sent to POND families with study information and contacts. Potential participants will be contacted by a research assistant until the recruitment target is reached.

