#### Feasibility

Feasibility measures include recruitment rate, retention rate, adherence rate, and success of randomization and blinding. Recruitment and attrition will be calculated using the electronic audit trail generated by the documentation kept by the independent RA and statistician and research assistant. Adherence will be calculated based on the number of sessions attended and completed by participants who complete all assessments. The success of blinding will be determined based on responses to the questions “What group do you think you were in?” and “How sure are you?”, which will be asked on the follow-up tolerability questionnaire (adapted from Garvey et al., 2001) [52]. Descriptive statistics will be completed to establish if the comparison and intervention groups are similar in age, gender, ASD severity, and clinical symptom severity. The success of randomization will be determined by evaluating group differences in sex distribution and median age. Randomization will be determined to be successful if the differences in sex distribution are within ± 2 participants, and the median age difference is within ± 2 years.

The feasibility of the optional MRI component will be evaluated based on total and successful attempts at completing the MRI protocol. There is a paucity of data on neural outcomes in this population; therefore, any amount of data collected is valuable. Previous MRI studies examining children with ASD include samples between 20 and 50 participants [53–57]. In a hypothetical sample size, *n* = 100 (*n* = 50 per group) for a full-scale RCT, including data from at least 20 individuals in each group would be sufficient to conduct an analysis. Given this, the optional MRI component of this study will be feasible if ≥ 20% of participants in each group have successful MRIs. A successful attempt is one in which a majority of the scan is completed with minimal motion artifact as determined by the MRI technician.

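### The clinical and Go/No Go models account for age only through the baseline score; prespecifying age as a covariate would be a minor, cheap improvement

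*Protocol article*

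**What the plan says.** The section Clinical and cognitive (under Secondary measures analysis) describes a linear mixed model for follow-up scores. Its terms are listed: "baseline and treatment allocation values will be included as fixed-effect predictors"; "Time points will be included as a fixed factor"; and "a random intercept will be included at the participant level". Neither age nor sex appears.

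Three other places bear on age:

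- Recruitment: children "aged 9–18 years will be recruited".
- Randomization and blinding: 1:1 allocation in permuted blocks of varying size. No stratification factor is named.
- Feasibility (under Primary outcome measures): "The success of randomization will be determined by evaluating group differences in sex distribution and median age". The limits are that "the differences in sex distribution are within ± 2 participants" and that "the median age difference is within ± 2 years". The same section plans descriptive statistics to "establish if the comparison and intervention groups are similar in age, gender, ASD severity, and clinical symptom severity".

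The model applies to the clinical scales and the Go/No Go task. Neural outcomes are treated separately, without a stated covariate set.

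**The concern.** The accepted median age gap of 2 years is 2/9, or 22%, of the recruited age range. No stated step prevents such a gap, and the outcome model takes up age only through its relation with the baseline score. Children of 9 and 18 may differ in how they change on a response-time and accuracy task, and the last follow-up is at week 18. Where age relates to change, the baseline score absorbs less of it.

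Two things are at stake. One is a shift in the estimates meant to indicate the likely size of the effect for a later trial. The other is an analytic choice left open: the plan states no consequence for the model if the balance check shows a gap, so a decision to adjust could be made after the imbalance is seen.

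**Working it through.** The plan has no figure of its own to reproduce here. It gives no age SD, outcome SD or correlation, so protocol inputs and assumptions are kept apart.

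**From the protocol article.** 46 children randomised 1:1, so 23 per arm; 10% expected loss, 46 × 0.90 = 41.4, taken as 42 analysed (21 per arm); ages 9–18; tolerance of 2 years on the median gap.

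**Assumed.**

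- Ages uniform on 9–18, so SD = 9/√12 = 2.60 years.
- Baseline to follow-up correlation r = 0.5–0.7.
- Either age correlates ρ = 0.1–0.4 with the score equally at both visits (level only), or age has a partial correlation p = 0.2–0.4 with the follow-up score given baseline (age also affects change).

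**Step 1: how often a gap arises.** The SD of the difference in mean age is 2.60 × √(2/23) = 0.77 years. In 200,000 simulated allocations the medians differ by 1–2 years in 32% and by more than 2 years in 12%. The latter figure is 16% for ages uniform on 9–19 and 3% for roughly normal ages with SD 2.4.

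**Step 2: from median gap to mean gap.** The shift depends on the mean gap, but the tolerance is on the median. Given a median gap of 1–2 years, the mean gap averages about 0.74 years. Among all allocations within the tolerance, the mean gap exceeds 1.5 years in only 1.3%. In units of age SD, g = 0.74/2.60 = 0.285.

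**Step 3: shift in the baseline-adjusted estimate, in outcome SD.**

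- Level only: ρ × g × (1 − r). Lowest 0.1 × 0.285 × 0.3 = 0.009; highest 0.4 × 0.285 × 0.5 = 0.057.
- Change: p × √(1 − r²) × g. Lowest 0.2 × 0.714 × 0.285 = 0.041; highest 0.4 × 0.866 × 0.285 = 0.099.

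Together this is about 0.01 to 0.10 SD. As a check on the level-only case, a simulated ANCOVA at one follow-up (21 per arm, r = 0.6, ages uniform on 9–19, median gap 1.5–2 years) gave shifts of 0.02, 0.04 and 0.05 SD for ρ = 0.2, 0.3 and 0.4 without age, and about 0 with age in the model.

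**Step 4: beside sampling error.** The 95% half-width at one follow-up is 1.96 × √((1 − r²) × 2/n):

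- r = 0.7, n = 23: 1.96 × √(0.51 × 2/23) = 0.41 SD.
- r = 0.5, n = 20: 1.96 × √(0.75 × 2/20) = 0.54 SD.

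The largest shift, 0.099 at r = 0.5, is about a fifth of the half-width (0.099/0.54 = 0.18).

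**Step 5: validity.** In the same simulation, over all randomisations, the mean estimate was about 0 and coverage about 95%, with or without age. Coverage without age was also about 95% in the subset with a median gap of 1.5–2 years.

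**Step 6: price of adding age.** With 42 analysed, one uninformative covariate multiplies the variance by about 38/37 = 1.027, so the standard error rises by √1.027 − 1 = 1.3%. With p = 0.4 the variance factor is (1 − 0.16) × 1.027 = 0.863 and the standard error falls by 7% (8% before the degree of freedom is paid for). Break-even is at p = √(1 − 37/38) = 0.16.

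**The case against.** The strongest case against raising this is that a mixed model adjusted for the baseline score is a standard choice and that nothing in the plan is wrong. In detail:

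- Under 1:1 randomisation a chance age gap is not bias, and the ordinary interval already allows for it. This stands.
- The limits in the Feasibility section check the randomisation process. They do not declare age or sex prognostic, and ASD severity and symptom severity are compared there too without becoming covariates. A reader might infer that the model contradicts the balance criterion; the documents do not support that.
- The outcomes are secondary and exploratory, and the progression criteria in Table 1 do not use the effect estimates. This stands and limits the weight of the point.
- A statistical analysis plan that is not shown may add covariates. That is possible. Still, the section lists its predictors and does not say that others follow.
- The age correlations are assumed. This also stands. If age relates only to level, the shift is at most about 0.06 SD and adjustment gains little precision.

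What survives is narrower: no stated step deals with age beyond the baseline score, and the plan does not say whether the model would change if the balance check failed.

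**Conclusion.** The point holds as a minor, inexpensive improvement to the clinical and Go/No Go models, not as an error. Given a median age gap of 1–2 years, the estimates can shift by about 0.01 to 0.10 SD, most if age affects change. This rests on ages uniform on 9–18, a baseline to follow-up correlation of 0.5–0.7 and the assumed age correlations.

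Three stronger readings are tempting and fail:

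- That an accepted imbalance passes unadjusted into every effect estimate. The baseline score removes 50–70% of the shift when age acts on level (the factor 1 − r is 0.5–0.3), and the model does not cover the neural outcomes.
- That the tolerance lets through shifts of 0.12–0.25 residual SD. Those figures belong to a mean gap of 1.5 years, which is rare among accepted allocations.
- That sex must be added as well. No figure in the documents shows a gain, and it would add about 1–2% to the standard error.

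**What to change.** In the section Clinical and cognitive, add age at baseline (continuous) as a fixed effect in the mixed model for each clinical and Go/No Go outcome. State that it is included whatever balance is observed, and report the model with the baseline score alone as a sensitivity analysis. Sex may be added but need not be.

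The cost is one or two sentences and one degree of freedom. The standard error grows by about 1% if age adds nothing beyond baseline, and precision improves only if the partial correlation exceeds about 0.16. Fixing the term before unblinding also removes the temptation to choose covariates after the balance check. The randomisation method and the feasibility limits need not change for this purpose.

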##### Neural

Structural and functional neuroimaging changes between timepoints T0, T1, and T2 will be compared between groups, and associations between baseline neuroimaging and treatment outcomes will be explored. Freesurfer (https://surfer.nmr.mgh.harvard.edu/) will be used to obtain cortical thickness from structural MRI data. MRtrix3 software will be used to process diffusion imaging data to determine changes in white matter tracts [76]. Blood-oxygen-level-dependent (BOLD) signal of resting-state functional MRI will be analyzed using the fMRIPrep pipeline. All results will be corrected for multiple comparisons using the false discovery rate (FDR) method (*P*_FDR_ < 0.05). Changes in network activity will be analyzed using the left DLPFC as a seed.

## Discussion

To establish the clinical effectiveness of home-based tDCS for self-regulation in ASD, a well-designed RCT is needed. However, efficacy RCTs are highly resource intensive [77]. This pilot RCT will provide critical insights that position an efficacy RCT for success and ensure that resources are invested in trials likely to generate clinically meaningful results [78].

The design of the current study is novel and addresses important limitations of previous studies. There is relatively limited research into the effects of tDCS on ASD in children with the findings reported in the existing literature being inconsistent and unconvincing. Several reviews and meta-analyses have concurred that there is a need for well-designed randomized, double-blinded studies with long-term follow-up measurements to increase the quality of evidence for tDCS [18, 36, 39, 46, 79]. Most existing studies are open-label or case reports, and fewer than half of the clinical trials utilized a sham-control group [36, 39]. Current research is also lacking in longitudinal data, which is important in evaluating the long-term safety and efficacy of tDCS. By including both 1-week and 18-week follow-up timepoints, this protocol allows for the evaluation of whether it is feasible to capture this longitudinal data.

This protocol minimizes many of the biases that are present in earlier tDCS studies. The use of randomization, double-blinding, and sham-control reduces performance and selection biases. While previous literature excludes individuals with low IQs [39], the lack of IQ cutoff in this study further reduces the barriers to participation and allows tDCS to be explored in a broader population. Additionally, the heterogeneous nature of neurodevelopmental disorders presents several challenges, particularly due to the common presence of comorbidities. By focusing on a subsample of the ASD population with self-regulatory issues, a common comorbidity is identified, addressing the potential bias of a non-homogeneous sample.

The secondary outcome measures of this study provide a comprehensive assessment of self-regulation and include measures that independently examine specific components of self-regulation (emotional regulation and response inhibition). This is necessary to capture the heterogeneity of behaviors in the ASD population and to determine which clinical measures are sensitive to treatment-related changes. Additionally, very few tDCS studies of self-regulation in ASD have examined neural changes and none have employed quantitative MRI techniques. Existing research has relied on caregiver and participant reports, without including any form of clinician assessment [39]. The inclusion of the CGI assessment in this study, in addition to the randomization and double-blinding, limits the susceptibility of the results to placebo effects.

There is a clear need for accessible and cost-effective treatment options targeting self-regulation in children with ASD. However, there are currently no published studies that investigate home-based tDCS for ASD. The home-based approach has the potential to significantly reduce the burden on families and caregivers and overcome barriers to participation.

